**Conclusions:**

In this feasibility randomized clinical controlled trial, we will compare the effects of SWL blocking alone, administration of OM alone, and a combined intervention with both in patients with RP. We present this study so that it may be replicated and incorporated into future studies at other institutions, as well as applied to additional inherited retinal dystrophies. The goal of presenting this protocol is to aid recent efforts in reducing the impact of sleeping disorders and other psychological disorders on the quality of life in patients with RP and recovering their self-autonomy. In addition, the results of this study will represent a significant step toward developing a novel low-cost therapy for patients with RP and validating a novel therapeutic target.

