### Statistical Analysis

#### Sample Size Calculation

A sample size estimation of 48 patients (n=12, 25%, per group) was calculated for a target power of 80% and considering an α (probability of rejecting a true null hypothesis) of 5% and an actual power of 80.02%. Cohen d was 1.2 [101]. Due to the possible overestimation of the effect size in pilot studies, an effect size of 0.6 (medium-high) was chosen for this study. We calculated a total sample size of 60 participants (a total of 15, 25%, patients per group), adding approximately 20% (3 more patients per group than before) to manage possible dropouts [102-105].

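### The plan adopts an effect size of 0.6, but its 12 per group and 80% power belong to d = 1.2; at d = 0.6 the power is about 29% (35% with 15 per group)

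*Protocol article*

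**What the plan says.** Everything is in one paragraph of the protocol article, under Sample Size Calculation.

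- Starting calculation: "A sample size estimation of 48 patients (n=12, 25%, per group) was calculated for a target power of 80"%, "considering an α (probability of rejecting a true null hypothesis) of 5"% and with "an actual power of 80.02"%. The effect size given next to these figures is a Cohen d of 1.2, taken from a cited source.
- Change of effect size: "Due to the possible overestimation of the effect size in pilot studies, an effect size of 0.6 (medium-high) was chosen for this study".
- Final number: 60 patients, 15 per group, described as 3 per group more than the previous figure, an allowance of about 20% for dropout.

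The paragraph does not name the test or say whether it is one-sided or two-sided. It also does not say whether 0.6 is on the same scale as the 1.2. The Conclusions of the abstract describe the study with the words "In this feasibility randomized clinical controlled trial".

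**The concern.** The required sample size varies roughly with the inverse square of the effect size, so halving the effect should about quadruple it. Here the effect is halved and the number stays at 12 per group. The rise to 15 is explained entirely by dropout, so the more cautious effect size never enters the calculation.

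An ethics committee, funder or replicating centre would read the paragraph as promising 80% power for a deliberately conservative effect. If the calculation belongs to 1.2, the trial is powered only for the effect that the authors themselves suspect is too large. It would then probably not detect the effect they say they chose. This matters because the article sets out to compare the combination with each single intervention and with no intervention, and its concluding section looks ahead to showing superiority.

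**Working it through.** **Inputs (Sample Size Calculation section):** α = 0.05; target power 80%, stated actual power 80.02%; effect sizes 1.2 and 0.6; 12 per group before and 15 per group after the dropout allowance; four equal groups. *Assumption:* two-sided test, because that reproduces the stated power and a one-sided test does not.

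**Formula.** Two-sample t test with n per group: df = 2n − 2, noncentrality δ = d·√(n/2), power = P(|T| > t(0.975, df)), where T is noncentral t with df and δ.

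**Step 1: reproduce the plan's figure.** With d = 1.2 and n = 12, df = 22, δ = 1.2·√6 = 2.94 and the critical value is 2.074. Power is **80.2%**, against 80.02% stated. With n = 11 it is 76.3%, so 12 is the smallest n that reaches 80%. A one-sided test would give 88.5%, which does not match. The dropout step also reproduces: 12/(1 − 0.20) = 15 per group, 60 in total. The printed design is therefore the d = 1.2 design.

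**Step 2: use the effect size said to be chosen, d = 0.6.**

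| n per group | δ | Power |
|---|---|---|
| 12 | 1.47 | 29.0% |
| 13 | 1.53 | 31.2% |
| 14 | 1.59 | 33.3% |
| 15 (no dropout) | 1.64 | 35.5% |
| 44 | 2.81 | 79.5% |
| 45 | 2.85 | 80.4% |

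The 3 extra patients per group are there to replace dropouts, so 29% is the planning figure and 35% is the upper limit. Reaching 80% needs 45 evaluable per group, 4 × 45 = 180 in total. With the plan's own 20% allowance, 45/0.80 = 56.25, or 57 per group and 4 × 57 = 228 in total.

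**Step 3: what the planned size can deliver.** The effect detectable with 80% power is d = 1.20 at n = 12 and 1.06 at n = 15. The half-width of a 95% confidence interval for one pairwise difference, in SD units, is t(0.975, 2n − 2)·√(2/n):

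- n = 12: 2.074 × 0.408 = 0.85
- n = 15: 2.048 × 0.365 = 0.75

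**Step 4: other readings of the paragraph.**

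- *One-sided test at d = 0.6:* 41% (n = 12) or 48% (n = 15).
- *0.6 as Cohen's f in a four-group one-way ANOVA* (noncentrality N·f²): at N = 48, 48 × 0.36 = 17.3 and power is 93%. N = 36 (9 per group) already gives 82%. Neither 12 per group nor 80.02% follows. With two groups f = d/2, so f = 0.6 is the same effect as d = 1.2 and would not be the reduction the sentence describes.
- *Largest pairwise d = 0.6 in a four-group ANOVA, most favourable pattern of means* (f = 0.3): 35% at N = 48 and 44% at N = 60.
- *Baseline adjustment with one follow-up measure,* effective d = 0.6/√(1 − r²): at n = 12, r = 0.5 gives 37%, r = 0.7 gives 50% and r = 0.87 gives 81%. A correlation of about 0.87 would be needed, and the paragraph claims none.

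**The case against.** The strongest objection is that 29% applies to an unadjusted comparison of two groups at one time point, whereas the Statistics section plans a linear mixed model for the hormones and Table 3 has saliva collected at baseline and weekly for four weeks. Suppose the effect is 0.6 in single-measurement SD units, the correlation ρ is the same between all visits, and the mean of the four post-baseline samples is analysed with baseline adjustment. The residual variance is then (1 + 3ρ)/4 − ρ² of the single-measurement variance. Power per contrast at 12 per group is 63%, 67%, 75% and 87% for ρ = 0.5, 0.6, 0.7 and 0.8; at 15 per group it is 74%, 78%, 84% and 93%.

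This stands as a limit on scope: the low figure should not be presented as the power of every salivary analysis. It does not rescue the paragraph. The correlations appear nowhere in the article and the calculation claims no gain from repeated measures. The primary outcome is defined as change from baseline to postintervention, and the two sleep questionnaires (also primary) are measured only at baseline and week 4.

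Two smaller objections are fair. A four-group ANOVA with f = 0.5 also gives about 80% at N = 48, so d = 1.2 is not the only effect size that could produce the figure; but 0.5 is not stated anywhere, and of the two effect sizes printed only 1.2 fits. And the article does not say how a non-significant result would be interpreted, so any specific misreading is conjecture; the inconsistency does not depend on it.

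The feasibility label can justify a small trial, but not an 80% power statement for an effect at which that power was not calculated.

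**Conclusion.** The concern holds. The sample size and the 80% power go with d = 1.2, and the adopted effect of 0.6 never changes them. For one pairwise contrast at a two-sided 5% level without covariate or repeated-measures gain, power at d = 0.6 is 29% with 12 evaluable per group and 35% with 15, about 45 to 50 percentage points below the stated figure. On that basis a true effect of 0.6 would be missed about two times in three. The number needed for 80% is 45 evaluable per group.

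This rests on a two-sided two-sample t test, which is inferred because it reproduces the plan's figure, and on reading 0.6 as Cohen d, the scale named in the preceding sentence. Neither a one-sided test nor the ANOVA readings of 0.6 reconciles the text. The paragraph must be corrected before the trial starts.

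**What to change.** Keep the sample size and correct the statement about it. Suggested text:

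> Twelve evaluable patients per group give 80% power, at a two-sided 5% level, only for a standardised difference of about 1.2 in a single pairwise comparison. For a difference of 0.6 the power is about 29% (35% if all 15 per group are analysed). Fifteen per group are enrolled to allow for dropout.

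Remove the sentence naming 0.6 as the design effect. As the article calls this a feasibility trial, state that results will be reported as estimates with 95% confidence intervals (half-width about 0.85 SD at 12 per group and 0.75 SD at 15), and that a non-significant result is not evidence of no effect.

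The cost is wording only: no extra patients, visits or assays, and the trial has not started. The published power becomes less favourable.

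If the sponsor prefers to keep 0.6 as the design effect with 80% power, the number has to be recalculated. On the assumptions above that means 45 evaluable per group, or 57 per group (228 in total) with the plan's 20% allowance. A smaller number from the mixed model would have to state and justify its assumed correlation, and would not carry over to the sleep questionnaires.

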#### Statistics

A linear mixed effect regression model will be applied to compare intervention arms against the control at baseline and stimulated measures for the HPA axis or the retinal–SCN–pineal axis comprising cortisol, melatonin, and sAA [106]. Baseline characteristics of patients from each group will be compared applying independent *t* tests, 2-way repeated-measures ANOVA, and the Fisher exact test. To grade the RP severity (by quantifying clinical features, the ETDRS score, and visual field deviation) and the primary outcomes, we will consider both to be continuous variables and apply a multiple linear regression model. For secondary outcomes, normally distributed variables will be statistically assessed via parametric tests, such as the *t* test or ANOVA, while nonnormal distributed variables will be assessed with nonparametric tests, such as the chi-square test or the Fisher exact test and the Mann–Whitney U test. A chi-square or Fisher test will be performed to compare STAI, PSQI, and ESS scores among groups.

Statistical associations between covariates and outcomes will be evaluated using the appropriate statistical methodology, as previously described. Multivariable linear regression models will be appropriately fitted to continuous data based on the distributions of those data. Multiple logistic regression models will be fitted for all dichotomous outcome variables. Appropriate variable selection methods and model fit statistics will be used to determine the best-fitting model to determine the effects of treatment after adjusting for significant effects of covariates.

Finally, any protocol amendment will be first submitted to the Institutional Review Board for approval. If the amendment changes anything about what is reported

on ClinicalTrials, then the study’s registration on ClinicalTrials will be updated accordingly.

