A draft intervention protocol will be developed for each group, covering preintervention, intervention, postintervention, and discharge settings based on the literature. A steering committee comprising ophthalmologists, opticians, nurses, psychologists, and the research team will be created to develop these protocols. Additionally, 2 ophthalmology residents will be included. Finally, 1 patient with RP, who is the current president of the Federation of Inherited Retinal Dystrophies’ Associations, will be included in the steering committee. The steering committee members are experts in their respective fields and have used the existing literature (summarized in the *Background and Rationale* section) to inform the inclusion of the different interventions in the protocols. The draft intervention protocols are presented in Table 1. Although the choice of each intervention in these protocols will be informed by the literature [7,28,30,36,51,57,67,75-82] and expert consensus of the steering committee, the study will assess the efficacy of combined interventions in sleep disorders and stress control in a large group of patients with RP. Before the intervention period, all patients will be asked to complete sleep diaries for 2 weeks. In addition, patients in the intervention groups (SWL, OM, SWL+OM) must complete them during the intervention period (30 days). Patients from the SWL and SWL+OM groups will wear SWL-restricting goggles in bright-light conditions and when using light-emitting diode (LED) electronic devices for the 30 days of intervention. Patients from the OM and SWL+OM groups will take 3 pills of Circadin 2 mg (OM) every evening at 10:00 P.M. with a margin of 30 minutes before and after.

A preintervention time of 1.5 years will be necessary for recruitment, informed consent, eligibility screening, and baseline data collection. Next, patients will be randomized to 4 groups in a 1:1 ratio. The treatment groups will include SWL with or without the use of OM. The control group will include patients who are eligible for the study but not willing to be randomized to an intervention sleep and stress management pathway. When the intervention phase (4 weeks) is over, all patients will be followed up for 6 months via standard monitoring. Figure 2 provides a summary of the RCT timeline.

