### Limitations

The limitations that may be encountered in the application of this clinical trial are likely to be related to the large phenotypic and genotypic variability found among patients with RP; the difficulties in recruiting patients who meet the eligibility criteria, especially those with enough visual acuity that allows them to use the filters; and the subjective nature of the results of the questionnaires. However, this could be overcome by a good baseline study that allows for proper analysis that considers possible confounding variables. However, a sleep-monitoring device could be used, such as second-generation multisensory sleep trackers, but their price would increase the cost of the study and there is still no validated device for this purpose, so for the time being, they have not been included in the study protocol [122].

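### Baseline characteristics are to be tested between arms with tests that do not fit the design, and no covariate adjustment is fixed independently of observed significance

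*Protocol article*

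**What the plan says.** The Statistics section of the protocol article states: "Baseline characteristics of patients from each group will be compared applying independent *t* tests, 2-way repeated-measures ANOVA, and the Fisher exact test". It names no repeated factor for the ANOVA and does not say which pairs of arms the t tests compare.

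There are four arms: in the Overview, "patients will be randomized to 4 groups in a 1:1 ratio". Table 3 gives one visit for baseline characteristics, V0. The text above that table puts baseline assessments at the screening visit. On either reading it is a single occasion.

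On adjustment, Statistics describes looking at associations between covariates and outcomes, applying variable selection, and estimating treatment effects after adjusting for the covariates whose effects prove significant. Covariates and Confounders lists candidates, including sleep quality before the intervention, but not the RP severity score. Statistics mentions a multiple linear regression involving RP severity and the primary outcomes, without saying that it is the model for comparing arms.

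Limitations says of patient heterogeneity, recruitment difficulty and subjective questionnaires that "this could be overcome by a good baseline study that allows for proper analysis that considers possible confounding variables".

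**The concern.** Between randomised arms, the null hypothesis of a baseline test is true by design. Its p-value measures how unusual the allocation was, not how far an imbalance could move the outcome comparison. That depends on the size of the gap and on how strongly the variable predicts the outcome. In arms this small the test is silent on moderate gaps and still flags some differences by chance.

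Two of the named tests do not match the data. An independent t test takes two groups, so four arms need an unspecified set of pairwise tests. A two-way repeated-measures ANOVA needs a within-patient factor, which age, sex, visual acuity or a questionnaire score taken once at V0 does not have.

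A p-value column that changes no result does little harm by itself. What matters more is that the article commits to no prognostic adjustment made regardless of what the data show. With 12 to 15 per arm, a covariate's observed significance is a weak guide to whether it should be in the model.

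**Working it through.** **Inputs.** From Sample Size Calculation: "A sample size estimation of 48 patients (n=12, 25%, per group) was calculated for a target power of 80" per cent; "an α (probability of rejecting a true null hypothesis) of 5% and an actual power of 80.02" per cent; "Cohen d was 1.2"; "an effect size of 0.6 (medium-high) was chosen for this study"; and "We calculated a total sample size of 60 participants (a total of 15, 25%, patients per group), adding approximately 20" per cent. Two-sided testing is assumed because sidedness is not stated. Fifteen per arm is the recruited number and applies if everyone enters the baseline table; 12 is the number before the dropout allowance.

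**The plan's own figure.** A two-sample t test at two-sided 5%, d = 1.2 and 12 per arm has power 80.21% (noncentral t; required n 11.94), close to the stated 80.02%. The dropout step gives 12/0.8 = 15 per arm and 48/0.8 = 60 in total. Both match, so the arm sizes are taken as intended.

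**Smallest observed gap that is flagged.** In pooled SD units this is t(0.975, 2n−2) × √(2/n):

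- n = 12: 2.074 × 0.408 = 0.85 SD
- n = 15: 2.048 × 0.365 = 0.75 SD

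**Chance gaps under randomisation, one variable and two given arms** (300,000 simulated comparisons, normal data, gap in observed pooled SD):

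| | n = 12 | n = 15 |
|---|---|---|
| Gap of at least 0.5 SD occurs | 23% | 18% |
| Share of those not flagged | 79% | 73% |
| Share of gaps of at least 0.8 SD not flagged | 20% | 0% |

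A check on the second row: flagged gaps make up 5% of all comparisons, so the unflagged share is (0.234 − 0.05)/0.234 = 79% and (0.181 − 0.05)/0.181 = 72%. If gaps are scaled by the true SD instead, gaps of at least 0.5 SD occur in 22% and 17% of comparisons, and 78% and 71% of those are unflagged. The range is therefore 71-79%. On that scale about 28% (n = 12) and 9% (n = 15) of gaps of at least 0.8 SD are unflagged.

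**True differences missed (1 − power).** These matter only if the arms differ systematically:

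| True gap | n = 12 | n = 15 |
|---|---|---|
| 0.5 SD | 78% | 74% |
| 0.6 SD | 71% | 65% |
| 0.8 SD | 53% | 44% |
| 1.0 SD | 35% | 25% |

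**False flags.** Each t test flags 5% of perfectly randomised comparisons. The number of tests per variable is not stated. Three comparisons with control would flag about 12% of variables, and all six pairs about 20%. Fisher's test is conservative here, at about 1.7% to 2.3% per test.

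**What an unflagged gap could do.** In an unadjusted comparison, the shift in a given sample is about the covariate-outcome correlation r times the gap. The article gives no r. With r = 0.5 assumed, gaps of 0.5 to 0.75 SD shift the difference by 0.25 to 0.37 SD. With r = 0.3 and the smaller gap it is 0.3 × 0.5 = 0.15 SD; with r = 0.7 and the larger gap, 0.7 × 0.75 = 0.52 SD. The effect size the article says it chose is 0.6.

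**The case against.** The strongest reply is that nothing in the analysis depends on these tests. A reader might infer that they decide which variables are treated as confounders, or that a non-significant result will be taken as proof of comparability. The article says neither. Statistics selects covariates through their association with outcome, Covariates and Confounders lists candidates without reference to any baseline test, and the remark in Limitations mentions no test. This reply stands: deleting the p-values alone would change no estimate.

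A reader might also infer that chance imbalance biases the comparison. Under randomisation it does not, because its variability is already in the standard error. The shifts above describe particular samples, and they shrink where the outcome is a change from baseline or the model includes covariates. This also stands.

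Nor is a repeated-measures ANOVA impossible before treatment. Two saliva samples within 24 hours and two weeks of daily sleep diary could each supply a within-patient factor. The fair criticism is that no such measure is named and that characteristics measured once have none.

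The claim that large imbalances pass unnoticed would be too strong as well. It holds for gaps around 0.5 to 0.6 SD, is near even for true gaps of 0.8 SD, and fails at 1.0 SD.

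Finally, a fixed covariate set is often left to the analysis plan. Here, however, the article itself states an adjustment rule, so the criticism concerns what it says and not an omission.

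**Conclusion.** The point holds in limited form. The planned baseline tests are uninformative for randomised arms and partly unsuited to the design. At 12 to 15 per arm they flag only observed gaps of about 0.75 to 0.85 SD or more, so 71-79% of chance gaps of at least 0.5 SD pass unflagged. These figures assume normal data, two-sided 5% tests and true randomisation. The substantive weakness is that the stated adjustment depends on observed covariate significance, so adjustment for baseline outcome and disease severity is not assured.

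The documents do not support the further claims that the tests steer covariate choice, establish comparability or bias the result.

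Overview and Eligibility place patients who decline randomisation in the control group, whereas Study Population and Randomization have all eligible consenting patients randomised. If controls are self-selected, their baseline differences may be systematic and the chance-imbalance figures do not apply to them. That is a separate and larger problem, which this point neither depends on nor resolves.

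**What to change.** 1. Replace the sentence on baseline tests with descriptive reporting by arm: mean and SD or median and IQR, counts, and standardised differences, without p-values.
2. Delete the repeated-measures ANOVA from the baseline comparison, or name the repeated pre-intervention measure it is meant for.
3. State that each arm comparison is adjusted for the baseline value of its outcome and for the baseline RP severity score, whatever balance or covariate significance is observed.

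All these variables are already collected and the trial has not started, so only wording changes. The cost is the loss of the p-value column and the use of one or two degrees of freedom in each model. The sample size is unaffected. The gain comes mainly from the third step; the first two remove tests that cannot answer the question asked of them. The composition of the control arm must be settled separately.

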##### Ancillary Tests

Visual field impairment (VFI) will be assessed using a Humphrey 750i visual field analyzer (Carl Zeiss) and the central 30-2 SITA fast strategy protocol. Only tests that met the criteria (low [<20%], false positive, false negative, and fixation loss parameters) were evaluated [84].

Optical coherence tomography (OCT) images, assessing the central retinal thickness (CRT), macular ganglion cell–inner plexiform layer (GCIPL) thickness, and retinal nerve fiber layer (RNFL), will be performed using Cirrus HD-OCT 5000 with AngioPlex OCT-A (Carl Zeiss Meditec V.10.0) and cube scans. Only images with a signal strength of >6 with no movement artifact will be included in the study.

Two consecutive optical coherence tomography angiography (OCTA) images will be obtained by a single skilled examiner. A foveal centered scan area of a 3×3 mm^2^ pattern will be used, and all scans will be analyzed using en face OCTA images generated automatically with the optical coherence tomography microangiography (OMAG) algorithm in Angioplex software (ZEISS). The foveal avascular zone (FAZ) area will be manually outlined and expressed as square millimeters.

The vascular density (VD) will be measured automatically by the software, which will quantify the VD of a local region of tissue according to the ETDRS subfields. We will analyze the VD of each ETDRS sector, the inner ring, and the full area in 3×3 mm^2^ rings and exclude OCTA images with a signal strength of <7 [12].

The axial length will be calculated using an IOLMaster 500 optical biometer (Carl Zeiss Meditec) to be used as a correcting variable in the analysis, if necessary.

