#### Secondary Outcome Measures

Secondary outcome measures include any clinical macular changes or retinal function measured with the ETDRS scale, CSV-1000 chart, and ancillary tests, such as the VFI, OCT, and OCTA. In addition, several patient-reported variables, such as self-recorded sleep diaries, perceived stress, and functional status will be recorded.

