#### Covariates and Confounders

Several variables will be measured as potential covariates, including preintervention sleep quality scores, concomitant procedures, medical comorbidities, alcohol use, antianxiety medications or other nonprescribed medications used to help with insomnia and anxiety relief, tobacco use, and nonsteroidal anti-inflammatory drug (NSAID) and others anti-inflammatory drug treatment. In addition, basic demographic information will be obtained.

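### The retinal secondary outcomes, examined before and after treatment, are given simple tests with no stated use of each patient's baseline value

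*Protocol article*

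**What the plan says.** All references are to the protocol article.

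- **Outcomes.** Secondary Outcome Measures: "Secondary outcome measures include any clinical macular changes or retinal function measured with the ETDRS scale". The same sentence adds the contrast chart, visual field, OCT and OCTA.
- **Timing.** The clinical row of Table 3 is ticked at V0, V4 and the 6-month visit. The text above the table says that ophthalmic outcomes are collected at the follow-up visits. The table does not list the individual retinal tests.
- **Replicates.** Ancillary Tests, under the screening visit: "Two consecutive optical coherence tomography angiography (OCTA) images will be obtained by a single skilled examiner".
- **Tests.** Statistics: "For secondary outcomes, normally distributed variables will be statistically assessed via parametric tests", with the t test and ANOVA as examples. Non-normal variables get chi-square, Fisher or Mann-Whitney U tests. The variant of the t test or ANOVA and the quantity analysed are not stated.
- **Repeated-measures methods.** A mixed model is named for cortisol, melatonin and amylase. The list of methods for comparing baseline characteristics includes "2-way repeated-measures ANOVA, and the Fisher exact test". Neither method is attached to the retinal outcomes.
- **Covariates.** Covariates and Confounders: "Several variables will be measured as potential covariates, including preintervention sleep quality scores". The list continues with comorbidities, substance use and medication, and contains no baseline retinal measure. Statistics adds multivariable regression, with covariates chosen by variable selection.

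**The concern.** The patient is the unit of randomisation, and each patient's retinal measures are due before treatment, at its end and at 6 months. The V0 value is likely to be the best single predictor of the later value. Entry covers moderate and severe disease, and the Limitations section itself expects wide variation between patients. It relies on a good baseline study to deal with that variation, yet the sentence on secondary outcomes does not say that the baseline value enters the comparison.

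If follow-up values alone were compared, the differences between patients that existed before treatment would remain in the error term, and a real retinal effect could be missed. With at most 15 patients per arm, that loss matters.

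The placement of the repeated-measures ANOVA adds to the doubt. A comparison of baseline characteristics between arms has no repeated factor, so the method has no use there. The outcomes that do have a repeated factor are given ANOVA without qualification.

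**Working it through.** **Inputs**

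- Two-sided 5% level. The article gives 5% and does not state sidedness.
- 12 per arm, and 15 per arm after the dropout allowance (Sample Size Calculation).
- Standardised difference d = 0.6, which that section says was chosen. It is not tied to any retinal measure and serves here only as a benchmark.
- Correlation r between the V0 and follow-up values. The article gives none, so r is an assumption, shown from 0.5 to 0.9.

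**Reproducing the plan's own figure.** The article states "Cohen d was 1.2", with 12 per group and an actual power of 80.02%. For a two-sided two-sample t test the noncentrality is d × √(n/2) = 1.2 × √6 = 2.94 on 22 degrees of freedom. The power is 80.2%, so the plan's figure is recovered with a comparison of one value per patient.

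**Three analyses of the same data.** Each is a comparison of two arms, with the follow-up SD set to 1 and equal SDs at both visits.

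- Follow-up value only: effective d = 0.6, df = 2n − 2.
- Change from V0: effective d = 0.6 / √(2(1 − r)), df = 2n − 2.
- ANCOVA on V0: effective d = 0.6 / √(1 − r²), df = 2n − 3.

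The noncentrality is effective d × √(n/2). With n = 15, √7.5 = 2.739. At r = 0.8, for example:

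- Follow-up only: 0.6 × 2.739 = 1.64.
- Change: (0.6 / √0.4) × 2.739 = 0.949 × 2.739 = 2.60.
- ANCOVA: (0.6 / √0.36) × 2.739 = 1.000 × 2.739 = 2.74.

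**Power, 15 per arm**

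| r | Follow-up only | Change | ANCOVA | ANCOVA minus change (points) |
|---|---|---|---|---|
| 0.5 | 35.5% | 35.5% | 44.8% | 9.3 |
| 0.7 | 35.5% | 53.5% | 60.2% | 6.7 |
| 0.8 | 35.5% | 70.8% | 75.2% | 4.4 |
| 0.9 | 35.5% | 94.4% | 95.3% | 0.9 |

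**Power, 12 per arm**

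| r | Follow-up only | Change | ANCOVA |
|---|---|---|---|
| 0.5 | 29.0% | 29.0% | 36.7% |
| 0.7 | 29.0% | 44.2% | 50.1% |
| 0.8 | 29.0% | 60.3% | 64.7% |
| 0.9 | 29.0% | 88.1% | 89.5% |

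Below r = 0.5 the change score does worse than the follow-up value alone: at r = 0.3 and 15 per arm, 26.9% against 35.5%. ANCOVA gives 38.3% there. Over the assumed range from 0.3 to 0.9, ANCOVA is the best of the three.

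**Dependence on d.** At d = 1.2 with 12 per arm, follow-up only has 80.2%, and ANCOVA has 89.9% at r = 0.5 and 99.7% at r = 0.8. The loss is then about 10 to 20 points.

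**The case against.** The strongest reply is that the sentence is open. The tests are given as examples, the word independent is used only for the baseline t tests, and ANOVA is unqualified. A t test, ANOVA or Mann-Whitney test on change from V0 uses one value per patient, is valid between arms and keeps the within-patient pairing. The macular outcome is itself worded as change. The covariate list is not exhaustive, and adjusted regression is planned. Finally, a condensed article may leave such detail to the analysis plan.

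Much of this stands, and it rules out three stronger readings that a reader might infer.

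- **That the plan prescribes independent-sample tests and so discards the pairing.** The text fixes neither the variant nor the quantity analysed.
- **That most of the power is lost.** At d = 0.6 this needs both that baseline is ignored and that r is about 0.8 or more. With 15 per arm, 35.5 / 75.2 = 0.47 of the power is kept at r = 0.8, but 35.5 / 60.2 = 0.59 at r = 0.7.
- **That two OCTA scans are taken at every visit and counted as separate observations.** The pair is described only among the screening tests, and nothing says that the two images enter as separate rows. No inflated false-positive rate can therefore be attributed to the plan.

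The reply does not remove the rest. The article is not silent: it names tests for these outcomes, and none of them is tied to the baseline value. The primary outcomes are defined as changes from baseline, but retinal function is not. Covariates that enter by selection do not guarantee that the V0 value is used. The repeated-measures ANOVA on baseline characteristics is an error in the text as it stands, whatever an analysis plan may add.

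**Conclusion.** The concern holds in a limited form. The article assigns simple tests to retinal outcomes measured before and after treatment, does not say that change or the V0 value is used, and puts its only repeated-measures ANOVA where there is no repeated factor.

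The cost depends on what is eventually analysed. With follow-up values alone, d = 0.6 and 15 per arm, the shortfall against ANCOVA is about 9, 25, 40 and 60 points at r = 0.5, 0.7, 0.8 and 0.9. With change scores it is about 9, 7, 4 and 1 points. These figures rest on assumed correlations, on equal SDs at both visits and on a d that the article does not link to any retinal measure.

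The point concerns secondary outcomes and does not touch the primary hormone model. It should be settled before the trial starts, because the choice between follow-up, change and adjusted values should not be open once data are seen.

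**What to change.** In the Statistics section, replace the sentence on tests for secondary outcomes, as far as it covers continuous retinal measures, with the following content.

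1. Reduce each outcome to one value per patient per visit. Average replicate OCTA scans where they are taken. Where both eyes are measured, use the patient mean or keep eye nested within patient.
2. Fit a linear mixed model with arm, visit (V4 and 6 months), arm-by-visit and the V0 value of the same outcome as a prespecified covariate, allowing for correlation between visits in the same patient. ANCOVA at each visit is an acceptable simpler form. Report the adjusted difference between arms at V4 and at 6 months.
3. For clearly non-normal outcomes, use the same model on transformed or ranked values.
4. Delete the repeated-measures ANOVA from the comparison of baseline characteristics.

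Add the baseline retinal values to the list in Covariates and Confounders so that the two sections agree.

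The cost is wording and a little programming. The clinical examination at V0 is already scheduled, no patient, visit or procedure is added, and the article states that the trial has not started.
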